### Covariates

We plan to include practice characteristics including the practice size and the deprivation score associated with the practice. The covariates to be included in the statistical model will consist of the age, sex, and ethnic group of the child. The baseline for the primary outcome of prescriptions, the number of asthma preventer prescriptions, will be the years 2019 and 2020 in August and September. To account for the effect of practice clustering, GP will be included as a random effect. The same covariates will be collected for both intervention and non-intervention arms in the study.

### Statistics

#### Sample size

The sample size is based on feasibility and the anticipated number of practices providing data to the CPRD. We anticipate a sample size of approximately 1389 GP practices (694 on intervention and 695 on control). Alongside this, from the previous study (PLEASANT), we also anticipate 85 school-age children having asthma per practice [14]. Assuming an expected rate of 30% of people collecting their prescription and an intraclass correlation of 0.03, it is anticipated that the precision of the estimates in the study—estimated as a half-width of a 95% confidence interval—will be 1%.

#### Data analysis

Statistical methods appropriate to a cluster randomised trial will be used for the analysis of the data. The statistical analysis will be performed on an intention-to-treat-basis and reported according to CONSORT guidelines for Cluster RCTs [17]. A dropout of practices is not expected. Some practices may merge, close, or split. Small numbers are likely to be involved, but no special treatment is necessary and no imputation is planned.

#### Primary analysis

The proportion of children having a preventer prescription collected within the primary time period per child will be analysed using a random effect logistic regression model with the individual’s age, sex, number of preventer prescriptions in the baseline period as covariates, the trial arm (intervention or control) as a fixed effect, and the design/cluster effect of general practice as a random effect. Effect sizes (assessed as an odds-ratio) and 95% confidence intervals for the primary endpoint will be presented. The number of prescriptions per child will be similarly analysed separately for each time period using negative binomial regression.

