### Randomisation and allocation concealment

Practices will be allocated 1:1 to intervention or control to ensure an equivalent sample size in each arm of the study in terms of the number of children with asthma. The randomisation will be stratified by the size of the practice as assessed by decile within the CPRD. All the practices in the study will be known from the CPRD and will not be prospectively recruited. GP practices randomised to the intervention will receive a postal bulletin and an email advising them to implement the study. GP practices randomised to control will not receive postal bulletin or email, and they will continue with usual care.

For practices included in the study, randomisation will be undertaken by study statistician using bespoke Excel spreadsheet. A file with anonymous practice identification codes and the stratification number will be provided to the CPRD. The statistician will not receive any information that would identify the practices.

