#### Trial status

The trial is now at the stage where we have received the routine data, and it is being processed and cleaned before analysis can begin.

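### The primary model leaves out the randomisation stratifier (practice-size decile), and the Covariates and Primary analysis sections disagree on ethnic group and leave size and deprivation unclear

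*Protocol article*

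**What the plan says.** Four places in the protocol article bear on this.

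- **Randomisation and allocation concealment:** "The randomisation will be stratified by the size of the practice as assessed by decile within the CPRD". The purpose given for the 1:1 allocation is "to ensure an equivalent sample size in each arm of the study in terms of the number of children with asthma".
- **Covariates:** for practices, "We plan to include practice characteristics including the practice size and the deprivation score associated with the practice"; for children, "The covariates to be included in the statistical model will consist of the age, sex, and ethnic group of the child". Baseline preventer prescriptions are also named (the baseline "will be the years 2019 and 2020 in August and September"), and practice is a random effect.
- **Primary analysis:** a random-effect logistic regression with "age, sex, number of preventer prescriptions in the baseline period as covariates, the trial arm (intervention or control) as a fixed effect". Clustering is handled through a random effect for practice. The result is reported as an odds ratio with a 95% confidence interval.
- **Trial status:** "we have received the routine data, and it is being processed and cleaned before analysis can begin".

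**The concern.** There are two separate matters.

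First, when randomisation is stratified by a factor that predicts outcome, the arms are balanced on it by design. The true sampling variance of the treatment effect is then smaller than an analysis that ignores the factor reports. The interval comes out too wide and the test rejects too rarely. The primary model as written has no term for the one factor used in stratification.

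Second, the two sections that describe the model do not give the same covariates, and nothing says which governs. With outcome data already delivered, more than one adjusted model could be presented as the planned one. The choice can also change what is estimated: an odds ratio from a logistic model is conditional on its covariates, so putting ethnic group in or out can shift the reported figure even when neither version is biased.

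**Working it through.** **Covariate lists side by side**

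| Term | Used in randomisation | Covariates section | Primary analysis section |
|---|---|---|---|
| Arm | – | – | yes |
| Age, sex | no | yes | yes |
| Baseline preventer prescriptions | no | yes | yes |
| Practice random effect | – | yes | yes |
| Ethnic group | no | yes, in the statistical model | no |
| Practice size | yes (deciles) | to be included, no model named | no |
| Practice deprivation | no | to be included, no model named | no |

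Ethnic group is a direct contradiction. For size and deprivation the Covariates wording can be read two ways. If it means model terms, the Primary analysis section contradicts it. If it means variables to be collected, the stratifier is in neither list. On both readings the primary model as written lacks it.

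The Subgroup analyses section does not resolve this. It adds ethnic group and practice deprivation quintile to the main model as subgroup variables, which might suggest they are not already there. But it treats age and sex in the same way, and those are in the model.

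**Reproducing the planned precision**

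Inputs from the Sample size section: 694 and 695 practices, m = 85 children per practice, p = 0.30, ICC = 0.03.

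- Children per arm: 694 × 85 = 58,990 and 695 × 85 = 59,075.
- Design effect: 1 + (85 − 1) × 0.03 = 3.52.
- Half-width for the difference between arms: 1.96 × √[0.30 × 0.70 × 3.52 × (1/58,990 + 1/59,075)] = 0.0098, or 0.98 points. This matches the stated 1%.

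**Effect of adding practice size**

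Let f be the share of between-practice variance that size alone explains. The documents give no value for f, so 0 to 0.30 is an assumed range.

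- Share of the variance of a practice mean that lies between practices: 0.03 / (0.03 + 0.97/85) = 0.724.
- Design effect with size in the model: 0.97 + 85 × 0.03 × (1 − f) = 0.97 + 2.55(1 − f).
- Adjusted half-width: 0.98 × r, where r = √[(0.97 + 2.55(1 − f)) / 3.52].
- Type I error of the analysis that ignores size: 2 × [1 − Φ(1.96 / r)].

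| f | Design effect | Half-width with size in model (points) | Excess width if size is omitted | Type I error if size is omitted |
|---|---|---|---|---|
| 0 | 3.52 | 0.98 | 0% | 0.050 |
| 0.05 | 3.39 | 0.96 | 1.9% | 0.046 |
| 0.10 | 3.27 | 0.94 | 3.8% | 0.042 |
| 0.20 | 3.01 | 0.91 | 8.1% | 0.034 |
| 0.30 | 2.76 | 0.87 | 13% | 0.027 |

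A practice-level simulation (stratified by decile, 4,000 runs per value of f) agrees. Type I error without and with the decile term was 0.056 and 0.057 at f = 0, 0.044 and 0.051 at f = 0.10, and 0.027 and 0.049 at f = 0.30. The simulation error near 0.05 is √(0.05 × 0.95 / 4,000) = 0.003. The empirical spread of the estimate was almost identical in the two analyses: at f = 0.30, 1.96 times the empirical standard error was 0.87 points in both. So stratification has already delivered the precision, and the model without size fails to report it.

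The calculation is on the risk-difference scale with equal practices of 85, as in the plan's own precision figure. It starts from the unadjusted ICC. The planned model is logistic and already adjusts for each child's earlier preventer prescriptions, so f should be read as what size explains beyond that baseline.

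**The case against.** The case against has several strong parts.

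- **Size may not be prognostic.** The article explains the allocation by balance in numbers of children and nowhere says that size predicts uptake. If it does not, nothing is lost. This stands, and the range must start at zero.
- **Baseline prescriptions may do the work.** They are in the primary model and may carry much of the difference in prescribing between practices. This also stands and pulls the gain towards zero.
- **The conflict over size and deprivation is not firm.** The sentence on practice characteristics names no model, and the next sentence, which does name one, lists only child-level variables. A reader might infer that the two sections define flatly different models on all three variables. The text supports that for ethnic group only.
- **A fuller plan may settle it.** A SAP not shown may hold the final covariate list, and analysis had not begun. That could make the matter harmless in practice. It does not remove the contradiction on ethnic group, which the article itself states.

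A reader might also infer that adjusting for practice factors is worth 8% to 28% more practices. That figure takes 10% to 30% of between-practice variance as explained by size and deprivation together. Deprivation is not a stratifier, the range has no source in the documents and excludes zero, and no allowance is made for baseline prescriptions. It is not established.

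**Conclusion.** The point holds in a limited form. From the text alone, the primary model has no term for the stratification factor, the two sections contradict each other on ethnic group, and the role of practice size and deprivation is left unclear with data already received.

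The cost in precision is conditional. With size alone explaining an assumed 0% to 30% of between-practice variance, the half-width would be 0.98 to 0.87 points, and the gain is smaller if baseline prescriptions already absorb part of it. Omitting size errs on the conservative side.

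A reader might infer bias, an inflated false-positive rate or a failed precision target. None of these follows: type I error is at or below 5%, stratification balances size between the arms, and the stated 1% is reproduced without any size adjustment. Nor does the article show that anyone has chosen, or intends to choose, a model after seeing results; it says only that data were in hand while two covariate lists stood. The unresolved list is the more important half of the point, because it needs no assumption about f.

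**What to change.** State the same primary model in the Covariates and Primary analysis sections: arm, practice-size decile (as used in randomisation), age, sex and baseline preventer prescriptions, with practice as a random effect. Say explicitly whether ethnic group and practice deprivation belong to that model or only to a sensitivity analysis. Record the decision, with a date, before allocation is linked to outcomes.

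The cost is a change of wording in the article and in any SAP. No new data are needed: size decile was used for randomisation, and the other variables are already planned. Nine extra parameters for the deciles are negligible with about 1,389 practices.

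### The primary model takes past prescribing only from each child's own count; adding the practice's mean baseline could narrow the interval at almost no cost, by an amount the documents do not fix

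*Protocol article*

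**What the plan says.** The Primary analysis section of the protocol article sets out a random-effects logistic model. Its covariates are the individual's age, sex and "number of preventer prescriptions in the baseline period as covariates, the trial arm (intervention or control) as a fixed effect", with general practice as a random effect. The Covariates section defines the baseline: "The baseline for the primary outcome of prescriptions, the number of asthma preventer prescriptions, will be the years 2019 and 2020", in August and September. That section also names practice size and deprivation as practice characteristics, and its wording leaves the list open. The practice's own past uptake appears in neither section. Randomisation is stratified by practice size decile only, so the design does not balance past uptake either.

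The Sample size section plans for "approximately 1389 GP practices (694 on intervention and 695 on control") and says "we also anticipate 85 school-age children having asthma per practice". It continues: "Assuming an expected rate of 30% of people collecting their prescription and an intraclass correlation of 0.03". The resulting precision, "estimated as a half-width of a 95% confidence interval", is given as 1%. The ICC is not said to be adjusted for baseline.

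**The concern.** In a cluster trial the precision of the arm effect depends heavily on how much the randomised units differ. A child's count over two short windows is a sparse measure. Its single slope is set almost entirely by differences between children within a practice. If practice habits (repeat-prescribing routines, recall systems) persist more strongly than one child's count predicts, that slope removes too little of the between-practice variation. A mean over about 85 children measures the habit much better, and the planned model already needs the same records.

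Precision matters here because the number of practices is set by feasibility and cannot be raised. The intervention is also one step removed from the parent, and acting on it is left to each practice. As an illustration only, suppose one practice in four acted and reproduced the earlier trial's 4-point absolute August increase. The diluted effect would be 4 × 1/4 = 1 point, about the size of the planned half-width. The subgroup analyses are built on the same main model.

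**Working it through.** **Inputs from the Sample size section.** Practices 694 and 695; m = 85 children per practice; p = 0.30; ICC = 0.03; 95% interval.

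**1. The plan's own figure.** Design effect = 1 + 84 × 0.03 = 3.52. Half-width = 1.96 × √[0.30 × 0.70 × 3.52 × (1/(694 × 85) + 1/(695 × 85))] = 1.96 × 0.00500 = 0.98 points. The stated 1% is reproduced.

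**2. Between-practice share before adjustment.** 85 × 0.03 / 3.52 = 2.55/3.52 = 72.4%. The remaining 27.6% is within practices.

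**3. Why the common slope is a within-practice slope.** Assume the baseline count has the same ICC as the outcome. Per practice, the information on the slope is then 3.52/3.52 = 1 from between practices and 84 × 0.97/0.97 = 84 from within. Between-practice differences carry about 1/85 of the weight.

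**4. What each model leaves.** Let s be the child-level and r the practice-level correlation between baseline and outcome. Neither is in the documents; the assumed ranges are s = 0.1–0.6 and r = 0.3–0.9. The correlation of observed practice means is R = 0.724r + 0.276s. Variance of the arm comparison, relative to no adjustment:

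- child count only: 1 − 2sR + s²
- practice mean added: 1 − R²
- difference: (R − s)² = [0.724(r − s)]². This is never negative, and is zero when r = s.

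The between-practice variance left by the child count alone is a fraction 1 − 2sr + s² of its unadjusted amount.

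| s | r | between-practice variance left by child count | half-width, child count only | half-width, practice mean added | narrower by |
|---|---|---|---|---|---|
| 0.1 | 0.5 | 0.91 | 0.947 | 0.903 | 4.6% |
| 0.3 | 0.5 | 0.79 | 0.890 | 0.878 | 1.3% |
| 0.5 | 0.5 | 0.75 | 0.849 | 0.849 | 0.0% |
| 0.1 | 0.8 | 0.85 | 0.925 | 0.779 | 15.7% |
| 0.3 | 0.8 | 0.61 | 0.816 | 0.735 | 10.0% |
| 0.5 | 0.8 | 0.45 | 0.716 | 0.683 | 4.5% |
| 0.6 | 0.8 | 0.40 | 0.670 | 0.654 | 2.3% |
| 0.1 | 0.9 | 0.83 | 0.917 | 0.720 | 21.5% |

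Example, s = 0.3 and r = 0.8: R = 0.579 + 0.083 = 0.662. Child count only gives 1 − 0.397 + 0.09 = 0.693; with the practice mean, 1 − 0.438 = 0.562. √(0.562/0.693) = 0.90. In variance terms, 0.693/0.562 = 1.23, like 23% more practices.

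At r = 0.6 and s = 0.1: R = 0.462 and √(0.786/0.918) = 0.926, or 7.4% narrower. So 1–7% describes r = 0.5–0.6 with s = 0.1–0.3, and 5–16% describes r = 0.8 with s = 0.1–0.5. Larger s gives less.

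**5. Check on a binary outcome.** Simulations used 1389 practices of 85 and an exchangeable logistic GEE, with and without the practice mean. With a realised ICC of 0.027–0.035, the standard error of the log odds ratio fell by 1.5–4.3% at r = 0.5, 5.3–8.6% at 0.7, 6.1–14.1% at 0.8 and 13.3–21.0% at 0.9. Another set, with a lower ICC (0.015–0.02) and a wider spread of child propensities, gave standard-error ratios of 0.968, 0.999 and 0.987 at r = 0.5, and 0.901, 0.951 and 0.992 at r = 0.8. No run showed a loss.

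**The case against.** The strongest case against is that nothing in the planned model is wrong. The random effect accounts for clustering, randomisation protects against bias, and past prescribing is already adjusted for. The 1% precision is met with no baseline adjustment at all. All of this stands, and it limits the point to efficiency.

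The gain also rests on two correlations the protocol does not give. A high practice-level value can be doubted: the Discussion says 2020 was not a standard year, and 2019 lies two years before the outcome. That stands too, and a gain near zero is possible. Even a good gain is modest in absolute terms. At s = 0.3 and r = 0.8, the effect detectable with 80% power (2.8 standard errors) moves from 2.8 × 0.816/1.96 = 1.17 points to 2.8 × 0.735/1.96 = 1.05 points.

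A reader might infer that 72% of the variance is left unexplained by the planned model. The documents do not support this. The 72% comes from an ICC with no covariates, and an uncentred child count also carries practice differences. In the table above it leaves between 0.40 and 0.91 of the between-practice part. Nor do the documents show that the planned interval is certainly wider than it need be.

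It can be said that covariate form belongs in a statistical analysis plan, and that the Covariates list is open. But the Primary analysis section names its covariates, so this is a stated choice. If the full plan already carries the term, the point falls away.

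Finally, a covariate defined on all school-age children with asthma in 2019 and 2020 would need a wider extraction. The cohort is children aged 4 to 16 on 1 September 2021 with asthma medication in the last 12 months. Those who have since passed 16 are outside it, and the youngest were about 2 in 2019. This stands and fixes how the covariate must be built.

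**Conclusion.** The point holds as a recommendation on efficiency. The primary model can under-correct for persistent practice differences, and a practice-level baseline mean would recover some precision. The expected narrowing of the 95% interval is 0% to about 21.5% over the assumed correlations. It is about 1–7% at a practice-level correlation of 0.5–0.6 with weak to moderate child-level correlation, and about 5–16% at 0.8 unless child-level correlation exceeds about 0.5. Apart from the degree or two of freedom it uses, the term does not widen the interval in the approximation, and it did not in the simulations.

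These figures assume equal practice sizes, a baseline ICC equal to the planning ICC, and the risk-difference scale. The simulations used GEE. The planned measure is a practice-conditional odds ratio from a random-effects model, so the percentages carry over only approximately. No claim of bias, of an invalid interval or of a missed precision target follows.

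**What to change.** Add one practice-level covariate to the model in the Primary analysis section, alongside the child's own count. It is the practice mean of the same August–September 2019 and 2020 baseline prescription variable, entered by year or averaged, computed over the children in the extracted cohort. Entering it by year lets the model give 2020 less weight. State how children with no record in a baseline window are handled, and apply that rule to both terms. Use the same covariate in the August, September and prescription-count analyses.

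Specify it before the outcome is analysed by arm. The Trial status section says the data were still being cleaned, so at that stage this was possible.

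The cost is one sentence, one derived variable from records the planned model already needs, and 1–2 cluster-level degrees of freedom out of about 1389. The practice-conditional odds ratio being estimated also changes slightly, and the report should say so.

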#### Secondary analysis

The secondary endpoints—the number of unscheduled contacts per child and the proportion of patients with unscheduled medical contact in the different time intervals—will be similarly analysed to the primary endpoint.

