### Data source

The data for this study will be routinely collected data extracted from the Clinical Practice Research Datalink—Aurum (CPRD Aurum) database. This database covers approximately 20% of the UK’s population, with over 1300 general practices participating [16]. CPRD Aurum is a database of de-identified patient data that can capture all medical contacts, from prescription requests to out-of-hours contacts, along with the reason for the contact. The data is contributed by general practices.

CPRD will extract data from primary care medical 6 months post-follow-up. The research team will receive all data fully anonymised and will not have access to any patient identifiable data.

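### Read literally, the contact outcomes take over a prescription baseline instead of one of their own, which costs some efficiency but not validity

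*Protocol article*

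**What the plan says.** The Primary analysis section says the primary outcome "will be analysed using a random effect logistic regression model", with age, sex and "number of preventer prescriptions in the baseline period as covariates", trial arm as a fixed effect and practice as a random effect. Prescription counts "will be similarly analysed separately for each time period using negative binomial regression".

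The Covariates section defines one baseline: "The baseline for the primary outcome of prescriptions, the number of asthma preventer prescriptions, will be the years 2019 and 2020 in August and September".

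The Secondary analysis section is a single sentence. It names "the number of unscheduled contacts per child and the proportion of patients with unscheduled medical contact in the different time intervals" and says these "will be similarly analysed to the primary endpoint". It gives no covariate list of its own. Under Secondary outcome measures, the contact outcomes run from 1 September to 31 December 2021, in total and by month.

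On availability, the Data source section describes "de-identified patient data that can capture all medical contacts". The Trial design section mentions extraction only for the six months after implementation. The Trial status section says the data had been received and were being cleaned before analysis.

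**The concern.** If the cross-reference is followed as written, a child's autumn contacts are adjusted for summer prescriptions. That covariate is mismatched twice: it is a different measure, and its calendar window (August and September) shares only September with the outcome window. A child's earlier contacts would ordinarily be expected to predict later contacts better than earlier prescriptions do, and the same is likely of practices.

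Efficiency matters here because the effect on contacts is likely to be small. The Background says that PLEASANT's effects were small. In TRAINS they may be diluted further, since each practice decides for itself whether to act on the letter.

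**Working it through.** **Inputs from the article (Sample size).** 694 and 695 practices; m = 85 children per practice; rate 30%; ICC 0.03; 95% confidence. The rate and ICC are stated for collecting prescriptions. None is given for contacts, so both are borrowed below as stand-ins. All correlations between past and current contacts are assumptions.

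**1. The article's own precision figure.** Design effect DE = 1 + 84 × 0.03 = 3.52. Children per arm: 694 × 85 = 58,990 and 695 × 85 = 59,075. Half-width = 1.96 × √[0.3 × 0.7 × 3.52 × (1/58,990 + 1/59,075)] = 0.0098, or 0.98 percentage points. The stated 1% is reproduced. It concerns prescriptions and says nothing about the contact outcomes.

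**2. Where the variance lies.** Between-practice share = m × ICC/DE = 2.55/3.52 = 72%. With an assumed contact ICC of 0.01 it would be 0.85/1.84 = 46%. So the practice-level correlation of past with current contacts largely drives any gain at ICC 0.03, and less so at 0.01.

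**3. Linear scale, against no baseline term.** Let rc and rs be the practice-level and child-level correlations of baseline with outcome. Then r = 0.724 rc + 0.276 rs, and the half-width is multiplied by √(1 − r²).

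| rc | rs | r | Multiplier | Half-width (points) |
|---|---|---|---|---|
| 0 | 0 | 0 | 1.00 | 0.98 |
| 0.3 | 0.2 | 0.27 | 0.96 | 0.94 |
| 0.5 | 0.4 | 0.47 | 0.88 | 0.86 |
| 0.7 | 0.6 | 0.67 | 0.74 | 0.73 |

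These gains are not the effect of the proposed change, because the planned model already contains prescriptions.

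**4. The relevant comparison: prescriptions already in the model.** One data set was simulated per scenario, with 1389 practices of 85 children and one baseline period. Poisson and logistic models were fitted with practice-clustered standard errors. The assumed practice-level correlations were 0.3, 0.5 and 0.7. The resulting child-level correlations of past with current contacts were 0.14, 0.31 and 0.51; those of prescriptions with contacts were 0.11, 0.15 and 0.19.

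| Outcome | Child-level r | SE, prescriptions only | + child's past contacts | + practice mean as well |
|---|---|---|---|---|
| Count | 0.14 | 0.01282 | 0.01247 (−3%) | 0.01232 (−4%) |
| Count | 0.31 | 0.01320 | 0.01214 (−8%) | 0.01192 (−10%) |
| Count | 0.51 | 0.01337 | 0.01070 (−20%) | 0.01046 (−22%) |
| Any contact (logistic) | 0.14 | 0.01866 | 0.01840 (−1%) | 0.01818 (−3%) |
| Any contact (logistic) | 0.31 | 0.01816 | 0.01774 (−2%) | 0.01749 (−4%) |
| Any contact (logistic) | 0.51 | 0.01710 | 0.01623 (−5%) | 0.01587 (−7%) |

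**5. Odds ratios from a random-intercept logistic model.** Conditioning on a prognostic covariate moves the odds ratio away from 1 and can raise its standard error. A large-sample calculation held the marginal rate at 30%, used log-odds slopes of 0 to 1.5 per SD of the covariate and rc of 0 to 0.7, and compared with no baseline adjustment. The standard error ratio ran from 0.80 to 1.32; the ratio of z statistics ran from 1.00 to 1.33. For example, with slope 1 and rc 0.3, the log odds ratio grows by a factor of 1.187 and its standard error by 1.12, so z rises by 1.187/1.12 = 1.06 although the interval is wider.

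**The case against.** The strongest reply is that nothing in the article says past contacts are left out. The word used is similarly, not identically, and the Primary analysis section uses the same word while switching to negative binomial regression for counts. The Covariates section ties its baseline to the primary outcome, so each contact outcome could by analogy take its own past value. Covariate lists for secondary outcomes are often left to a statistical analysis plan. This stands in part: the exclusion of past contacts is an inference. But the article does fix a model for contacts by pointing to one with a named, outcome-specific covariate, and the generous reading still leaves the contact baseline without a period or a year. Two analysts could fit different models and both claim to follow the text.

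A reader might infer that the planned intervals are wider than the data allow. The documents do not support that. The correlations are assumed, the ICC belongs to prescriptions, and for the proportion outcomes a better model may give a wider odds-ratio interval.

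A reader might also infer bias from chance differences in practice contact rates. Randomisation and the practice random effect keep the comparison valid, and such differences are already reflected in the interval.

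Availability is also a fair objection. The prescription baseline needs 2019 and 2020 records, so the data must reach back beyond the stated six months. Whether autumn contacts from those years are included is not stated. The Discussion also describes 2020 as atypical, so that year may predict poorly.

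**Conclusion.** The point holds as one of efficiency and clarity for secondary outcomes. Taken literally, the contact analyses are adjusted for a covariate mismatched in measure and in calendar window, and a matching baseline should serve them better.

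With prescriptions already in the model, the simulated reduction in standard error from the child's own past contacts was about 3% to 20% for counts and 1% to 5% for logistic models; with the practice mean also included it was 4% to 22% and 3% to 7%. These figures rest on assumed correlations and single simulated data sets, with Poisson and clustered logistic fits standing in for the planned models. If past contacts did not predict current ones, the gain would be nil. For odds ratios the benefit should be described as power. The primary analysis is unaffected.

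**What to change.** In the Secondary analysis section, state that each contact outcome is adjusted for the child's count of the same contact type in the matching calendar months of 2019 and of 2020, plus the practice mean of that count, alongside age, sex and the practice random effect. Enter the two years as separate terms, because 2020 was atypical. That section names only unscheduled contacts; extending the rule to the all-contact and respiratory outcomes is a recommendation for consistency.

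Apply this if the records are held. First confirm that contacts for September to December 2019 and 2020 are in the CPRD extract already received. The text change is one sentence. The work is running the scheduled/unscheduled code list on the earlier records and setting a rule for children without a record in those years. If the contacts were not extracted, a supplementary extraction is needed, and the trial team would have to decide whether it falls under the Protocol amendments section. The choice should be fixed before the contact outcomes are analysed by arm.
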